### HCP’s involvement

#### Registration phase

After a short registration procedure that takes place during their first visit to the web-based app, the HCPs can continuously interact with it throughout the duration of the study. HCPs are given a short in-app training session.

#### Main usage phase

During the main usage of the MyPal web-based app, the HCPs can access symptom related data being stored in the system backend which had been collected by (1) the MyPal Child app and (2) the MyPal Carer app. HCPs are authorised to solely access the data of the patients of their associated clinical centre. The individual data of participating patients are reviewed by the associated HCP at least once every 72 hours to check for new entries. The data review and any action related to this are recorded through the web interface. The functionalities of the MyPal web-based app are outlined in table 4. All of them can be accessed by the HCP at any time. In addition, the HCP can use the MyPal Carer app in order to complete questionnaires as a proxy for one of their patients.

**Table 4 T4:** The functionalities of the MyPal web-based app offered to the HCPs

	Functionality	Description
H1	Incoming information summary	A central page of the web-based app displays in a summarised form the incoming patient information that has not been reviewed yet. Incoming information is automatically prioritised in the system using custom algorithms whereby pieces of incoming information are assigned the highest priority and placed at the top of the list. Whenever an item is reviewed in full, it is removed from the list.
H2	Individual data dashboard	A page that presents all the information collected for a given patient since the start of their participation in the study, using a dashboard with modern visualisations (see figure 4). The information includes primarily the patient’s responses to the symptom questionnaire along with additional clinical information (eg, treatment, age group, diagnosis group, etc.).
H3	Symptom Status over Time	This functionality and its visualisation are linked to the individual data dashboard. HCPs can document interim reports on current or past symptoms at different points in time as well as corresponding measures taken via selection of pre-defined choices. Additionally, the current or retrospective status of the patient’s disease as well as the goal of treatment can be updated considering the whole course of the study.
H4	Aggregated data dashboard	A page that presents aggregated and summarised information coming from all patients that participate in the study (descriptive statistics such a min, max, average and percentiles) using an analytics dashboard with modern visualisations.
H5	HCP response log	A page that is used for logging potential responses (eg, referral to a specialist or prescription of medical examinations) of the HCP to the presented information of a specific patient. The HCP can log any actions taken after visiting individual data dashboard of a patient in a structured manner.

**Figure 4 F4:**
[figure not shown]
Symptoms reported by study participants can be visualised in the MyPal web-based app for HCPs to be reviewed according to adjustable settings.

### Data collection and analysis

All applicable national and European Union (EU) legislation, particularly the General Data Protection Regulation (EU 2016/679)^20^ for the protection of individuals have been considered in the design of the study-related Information Technology (IT) infrastructure with regard to the confidential processing, collection and access to personal data. The technical deployment of the MyPal platform comprises of local server installations at each of the clinical study sites and one central server installation at the sponsor’s site distinctly defining premises of data accessibility. The data security concept entails regular synchronisation of only anonymised data from local to central database. The apps being installed on mobile devices are protected by confidential credentials and store encrypted data only temporarily locally in case of absent internet connection until they are deleted from the mobile device subsequent to transmission to the respective databases.

### Sample size calculation

Assuming relatively acceptable values for the attrition rate (ie, 20%) and the missing data (ie, 30%), the sample size analysis concluded that 100 recruited paediatric patients providing one measure at enrolment (baseline) and six repeated measures (at Months 1, 2, 3, 4, 5, 6) are sufficient for the power of the intended statistical testing to be over 90% in all cases, given (1) a 0.05 significance level and (2) an effect size of 0.1; the employed value of the effect size was based on a priori knowledge of the domain, all power calculations were performed using the G*Power statistical analysis software.^21^

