### Objectives and outcome measures

#### Primary objective

The main objective is to assess the feasibility and acceptability of a comprehensive, patient-centred service for palliative care in peadiatric oncology by adapting and advancing ePRO systems.

The corresponding primary outcome measures are the rates of recruitment, participation, adherence and premature discontinuation to the different components of the MyPal digital health platform during study enrolment. Further primary outcome measures are quantitative and qualitative data to be collected as follow-up to study enrolment: quantitative data from parents through the standardised System Usability Scale (SUS)^11^ as well as from the children through a newly adapted version of the SUS; qualitative data through structured interviews and focus groups with participants to identify further barriers, facilitators, preferences and engagement with regards to the MyPal digital health platform as well as differences between the participating clinical sites.

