### Data analysis

The subsequent analysis and evaluation will serve to assess the feasibility of the MyPal digital healthcare platform which uses ePROs to be ideally beneficial and supportive for the child and parents in palliative care.

Subgroup analysis of the outcome measures will be performed at baseline, month 3 and month 6 of the study using one-way, two-way and three-way analysis of variance (ANOVA) in order to detect potential differences between specific groups of participants. The level of significance for all statistical tests is set to a=0.05, in accordance with the power calculations. The grouping variables that will be assessed are (1) the clinical centre (origin), (2) the country of residence, (3) the age group, (4) the disease category (leukaemia, solid tumour, brain tumour), (5) the disease stage and (6) the starting point of the study in relation to the date of diagnosis. The latter point refers to recruited patients who have been under treatment for more than 6 months receiving care at the respective participating clinical site. These patients constitute a cohort for retrospective baseline data collection: the data collected from their completion of the ePROs at the beginning of their study enrolment will later be compared with outcome measure data derived from prospectively recruited patients whose treatment started within the last 6 months. Both groups will be followed likewise during the course of the study. Further data, like the daily number of steps (estimated by the smartphone/tablet using the measurements of the built-in sensors) as well as the documentation of the symptom status over time, will be used to examine the feasibility to assess for correlations with reported symptoms and reported physical activity.

To evaluate the changes in outcome measures over time in the child cohort, repeated measures ANOVA will be applied on each measure (or a non-parametric equivalent). Post hoc analysis will be applied as appropriate. Since wording and layout of questionnaires were partly modified compared with the validated versions for electronic completion and gamification, another focus is (or would be) to assess the feasibility of such modifications to the original questionnaires. Repeated measures multivariate ANOVA (MANOVA) will be applied to the QoL of the children and the parents which serve as a pair of dependent variables.

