To examine potential QoL differences between the participating sites, independent-samples t-tests and analysis of covariance (ANCOVA) models will be applied that will control for baseline criterion scores and potential confounders such as age group and sex which may be imbalanced between groups and associated with outcomes of interest.

The potential effect of the attrition is going to be assessed according to the methods introduced in Fewtrell *et al*,^22^ for example, comparison of baseline characteristics of seen versus not seen at the follow-up participants to assess potential bias, sensitivity analysis, re-evaluation of the power of the study with the attained sample size. The impact of missing data in the attempted analysis is going to be evaluated based on the importance of the variables. Checks for data ‘missing at random’ and ‘missing completely at random’ are going to be performed.

Additional quantitative feedback will be gathered by a final evaluation of the MyPal digital health platform based on an appropriate usability one-time scale, that is, SUS for patients or parents, whereas HCPs’ feedback will be collected via a designed web-based questionnaire at the end of the study.

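### Power of over 90% is claimed for every intended test, but the unadjusted single-visit group comparisons cannot reach it at an effect size of 0.1

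*Protocol article*

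**What the plan says.** The Sample size calculation section assumes 20% attrition and 30% missing data. It reports that "the sample size analysis concluded that 100 recruited paediatric patients providing one measure at enrolment (baseline) and six repeated measures" at Months 1 to 6 "are sufficient for the power of the intended statistical testing to be over 90% in all cases", at a 0.05 significance level and an effect size of 0.1, computed in G*Power. It names neither the metric of the 0.1 nor a within-child correlation.

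The Data analysis section lists the tests. Subgroup comparisons at baseline, month 3 and month 6 are made "using one-way, two-way and three-way analysis of variance (ANOVA) in order to detect potential differences between specific groups of participants". The grouping variables include clinical centre (three sites), country (two) and disease category (three). For sites it adds: "To examine potential QoL differences between the participating sites, independent-samples t-tests and analysis of covariance (ANCOVA) models will be applied". Changes over time in the children are tested by repeated-measures ANOVA, and the children's and parents' quality of life jointly by repeated-measures MANOVA. The same section links all of these to the sample size work: "The level of significance for all statistical tests is set to a=0.05, in accordance with the power calculations".

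**The concern.** The power statement covers every intended test, so one intended test that falls short refutes it. Cohen's f of 0.1 is a small effect. A comparison of groups at one visit uses one value per child and gains nothing from the six further measurements. With 100 children, such a test would not be expected to come near 90%.

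This figure is the only justification that the article gives for recruiting 100 children. The Data analysis section also plans to re-evaluate power at the attained sample size, and that exercise would start from a figure that does not hold.

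**Working it through.** **Inputs from the article.** N = 100 recruited; 7 measurements per child (baseline plus six); attrition 20%; missing data 30%; alpha 0.05; effect size 0.1; two groups (country) or three groups (site, disease category).

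**Assumptions.** Tests are F tests or two-sided t-tests. After attrition N = 100 × 0.8 = 80. If the missing data also removes whole children and the two losses multiply, N = 80 × 0.7 = 56. The article does not say this. Baseline comparisons are not reduced by attrition.

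**Attempt to reproduce the stated figure.** G*Power's formula for one-way ANOVA uses the noncentral F with λ = N × f² and k − 1 and N − k degrees of freedom. Taking 0.1 as f:

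| N | λ | 2 groups | 3 groups |
|---|---|---|---|
| 100 | 1.00 | 16.8% | 13.0% |
| 80 | 0.80 | 14.3% | 11.2% |
| 56 | 0.56 | 11.4% | 9.2% |

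None is near 90%. Reaching 90% at f = 0.1 would take 1,053 children for two groups and 1,269 for three. Two-way and three-way models test the same main effects with fewer error degrees of freedom, so at the same f they do no better.

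**Site t-test.** For two equal groups f = 0.1 corresponds to d = 0.2. With equal sites (assumed), each has about 100/3 ≈ 33 children. The noncentrality is 0.2 × √(33 × 33/66) = 0.81, and power is 12.6%.

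**More generous readings of 0.1.** With f² = 0.1, λ = 0.1N. With eta² = 0.1, f² = 0.1/0.9 = 0.111.

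| Reading | Groups | N = 100 | N = 80 | N = 56 |
|---|---|---|---|---|
| f² = 0.1 | 2 | 87.9% | 79.8% | 64.2% |
| f² = 0.1 | 3 | 80.3% | 70.0% | 52.8% |
| eta² = 0.1 | 2 | 91.0% | 83.8% | 68.8% |
| eta² = 0.1 | 3 | 84.5% | 74.8% | 57.5% |

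Only one of these twelve cells passes 90%: two groups, eta-squared, no losses. The three-group tests fail under every reading.

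**Baseline-adjusted ANCOVA.** With f = 0.1 scaled to f²/(1 − r²) for a covariate correlation r, power runs from 10.7% (three groups, N = 56, r = 0.5) to 62.2% (two groups, N = 100, r = 0.9).

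**Repeated-measures ANOVA, time effect.** λ = N × 7 × f²/(1 − ρ), with 6 and 6(N − 1) degrees of freedom and sphericity assumed. At f = 0.1 and ρ = 0.5, λ = 14.0, 11.2 and 7.84 for N = 100, 80 and 56, and power is 80.8%, 69.6% and 51.2%. Power reaches 90% when ρ is about 0.60, 0.68 and 0.78 respectively. If 0.1 is f², power is above 99% at ρ = 0.5 even with 56 children.

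**The case against.** The strongest defence is that the section describes a repeated-measures design, with a baseline and six further measures, and that the claim may be true for that test. This stands as far as it goes. The article gives no correlation, and a value of 0.60 to 0.78 or more, or a larger reading of 0.1, carries the time effect past 90%. A reader might infer from 51 to 81% power at a correlation of 0.5 that this calculation is wrong too. The document does not support that, because the 0.5 is not the protocol's figure. The defence does not save the claim as worded, however. It speaks of all the intended testing, the Data analysis section ties every test to the power calculations, and the single-visit comparisons do not depend on that correlation.

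Other points limit the size of the problem. The metric is unnamed, so the 9 to 17% range holds only if 0.1 is Cohen's f. The 56 children rest on an assumed product of losses; the missing data may mean missed monthly entries. Adjusting for baseline raises power, and under an f-squared reading with a useful covariate ANCOVA can pass 90%. That helps ANCOVA but not the unadjusted ANOVAs and t-tests.

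Finally, this is a feasibility study. "The corresponding primary outcome measures are the rates of recruitment, participation, adherence and premature discontinuation", together with usability and qualitative data, and the group ANOVAs are described as subgroup analyses. A reader might infer that non-significant subgroup results will be reported as showing no difference, or that 100 is the wrong sample size. The article says neither, and the calculation shows neither.

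**Conclusion.** The universal power claim is wrong for the unadjusted single-visit comparisons between groups. Under Cohen's f = 0.1, ANOVA power is 11.4 to 16.8% for two groups and 9.2 to 13.0% for three. The two-site t-test has 12.6% with 33 children per site. No reading of 0.1 that was tried brings the three-group tests to 90%; the best case is 84.5%, with no losses at all. With f = 0.1, ANCOVA remains between about 11% and 62% for covariate correlations of 0.5 to 0.9.

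The failure of the claim does not depend on the assumed losses, since it already fails with all 100 children; only the lower ends of the ranges use 80 or 56. The time effect in the repeated-measures ANOVA is left open: it is neither confirmed nor refuted without the metric and the correlation. The error concerns the justification given for the inferential tests, not the primary feasibility outcomes.

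**What to change.** In the Sample size calculation:

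- Delete the words *in all cases* and name the effect-size metric.
- Limit any power statement to the within-child time effect, and give the analysed N and the correlation actually used in G*Power.
- For the unadjusted comparisons between groups, state the effect detectable with 90% power. For three groups this is f of about 0.36 at N = 100, 0.41 at N = 80 and 0.49 at N = 56. For two sites of 33 it is d of about 0.81.

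In the Data analysis section, label these subgroup comparisons exploratory and remove the suggestion that the power calculations cover all tests.

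As an option, add the precision of the primary rates. For a rate with the 100 enrolled children as denominator, the 95% interval half-width is at most 1.96 × √(0.5 × 0.5/100) = 0.098, about 10 percentage points. This does not apply to the recruitment rate if its denominator is the children approached.

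The cost is a rewording and a less favourable stated figure. No extra patients are needed.

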### Data analysis

The subsequent analysis and evaluation will serve to assess the feasibility of the MyPal digital healthcare platform which uses ePROs to be ideally beneficial and supportive for the child and parents in palliative care.

Subgroup analysis of the outcome measures will be performed at baseline, month 3 and month 6 of the study using one-way, two-way and three-way analysis of variance (ANOVA) in order to detect potential differences between specific groups of participants. The level of significance for all statistical tests is set to a=0.05, in accordance with the power calculations. The grouping variables that will be assessed are (1) the clinical centre (origin), (2) the country of residence, (3) the age group, (4) the disease category (leukaemia, solid tumour, brain tumour), (5) the disease stage and (6) the starting point of the study in relation to the date of diagnosis. The latter point refers to recruited patients who have been under treatment for more than 6 months receiving care at the respective participating clinical site. These patients constitute a cohort for retrospective baseline data collection: the data collected from their completion of the ePROs at the beginning of their study enrolment will later be compared with outcome measure data derived from prospectively recruited patients whose treatment started within the last 6 months. Both groups will be followed likewise during the course of the study. Further data, like the daily number of steps (estimated by the smartphone/tablet using the measurements of the built-in sensors) as well as the documentation of the symptom status over time, will be used to examine the feasibility to assess for correlations with reported symptoms and reported physical activity.

To evaluate the changes in outcome measures over time in the child cohort, repeated measures ANOVA will be applied on each measure (or a non-parametric equivalent). Post hoc analysis will be applied as appropriate. Since wording and layout of questionnaires were partly modified compared with the validated versions for electronic completion and gamification, another focus is (or would be) to assess the feasibility of such modifications to the original questionnaires. Repeated measures multivariate ANOVA (MANOVA) will be applied to the QoL of the children and the parents which serve as a pair of dependent variables.

To examine potential QoL differences between the participating sites, independent-samples t-tests and analysis of covariance (ANCOVA) models will be applied that will control for baseline criterion scores and potential confounders such as age group and sex which may be imbalanced between groups and associated with outcomes of interest.

The potential effect of the attrition is going to be assessed according to the methods introduced in Fewtrell *et al*,^22^ for example, comparison of baseline characteristics of seen versus not seen at the follow-up participants to assess potential bias, sensitivity analysis, re-evaluation of the power of the study with the attained sample size. The impact of missing data in the attempted analysis is going to be evaluated based on the importance of the variables. Checks for data ‘missing at random’ and ‘missing completely at random’ are going to be performed.

Additional quantitative feedback will be gathered by a final evaluation of the MyPal digital health platform based on an appropriate usability one-time scale, that is, SUS for patients or parents, whereas HCPs’ feedback will be collected via a designed web-based questionnaire at the end of the study.

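### The named repeated-measures ANOVA and MANOVA use only complete series, which fits badly with the plan's own 20% attrition and 30% missing data

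*Protocol article*

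**What the plan says.** The Sample size calculation section plans for "100 recruited paediatric patients providing one measure at enrolment (baseline) and six repeated measures (at Months 1, 2, 3, 4, 5, 6"), that is, seven measures per child. It begins "Assuming relatively acceptable values for the attrition rate (ie, 20%) and the missing data (ie, 30"%), and concludes that this number is "sufficient for the power of the intended statistical testing to be over 90% in all cases". The conditions attached are alpha 0.05 and effect size 0.1, with no metric named for the latter. It does not say whether the 30% counts children or assessments, or whether it includes the 20%.

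The Data analysis section then names the longitudinal methods. For each measure, "repeated measures ANOVA will be applied on each measure (or a non-parametric equivalent"); the non-parametric test is not named. For the paired outcome, "Repeated measures multivariate ANOVA (MANOVA) will be applied to the QoL of the children and the parents which serve as a pair of dependent variables". Separately, "Subgroup analysis of the outcome measures will be performed at baseline, month 3 and month 6 of the study"; the method there is ANOVA.

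The end of the same section addresses missingness. It plans to compare baseline characteristics of participants seen and not seen at follow-up, to run a sensitivity analysis, to re-evaluate power with the attained sample, and to check whether data are missing at random or completely at random. No mixed model, estimating-equation method or imputation is named.

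**The concern.** Classical repeated-measures ANOVA, a Friedman-type test and repeated-measures MANOVA all work on complete rows. A child who misses one month contributes nothing, and in the MANOVA a gap in the parent's series also removes the pair. The article thus predicts incomplete series and names methods that cannot use them.

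Two things are at stake. The first is precision: the number analysed may be well below 100, and months that were reported are thrown away. The second is bias: if missingness depends on how ill or how engaged a child is, the completers differ from the cohort, and the estimated change in quality of life describes them rather than the recruited children.

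**Working it through.** **Inputs from the article:** 100 recruited children; baseline plus six monthly measures (m = 7); attrition 20%; missing data 30%; alpha 0.05; effect size 0.1; power over 90%.

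**Assumptions, since the article does not give them:** the effect size is Cohen's f; within-child correlation ρ is 0.5 or 0.8; sphericity holds; clustering of missed assessments follows a beta-binomial distribution.

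**Step 1: the plan's own power figure.** Within-subject test: λ = f²·N·m/(1−ρ), df1 = m−1 = 6, df2 = (N−1)(m−1), noncentral F.
- N = 100, ρ = 0.5: λ = 0.01 × 100 × 7/0.5 = 14, power 0.81.
- N = 80 (after attrition), ρ = 0.5: power 0.70.
- N = 56 (= 100 × 0.8 × 0.7), ρ = 0.5: power 0.51.

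The stated 90% is therefore not reproduced at ρ = 0.5. Reaching it needs an unstated ρ of at least 0.60, 0.68 and 0.78 respectively.

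**Step 2: children with all seven measures, out of 100.**

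| Reading of the 30% | Calculation | Complete children |
|---|---|---|
| Per assessment, independent, all 7 visits | 80 × 0.7⁷ | 6.6 |
| Per assessment, independent, baseline always present | 80 × 0.7⁶ | 9.4 |
| Per post-baseline assessment, including linear attrition | 80 × 0.7925⁶ | 19.8 |
| Per assessment, clustered, ICC 0.2 / 0.4 / 0.6 (6 visits) | 80 × B(a+6, b)/B(a, b) | 20.8 / 30.8 / 39.8 |
| Per assessment, clustered, ICC 0.9 | same | about 52 |
| Per child, after attrition | 100 × 0.8 × 0.7 | 56 |
| Per child, including attrition | 100 × 0.7 | 70 |

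In the clustered rows a = 0.7(1−ICC)/ICC and b = 0.3(1−ICC)/ICC. In the third row, linear attrition accounts for 0.2 × 21/36 = 0.1167 of the assessments, so the remaining completion rate is 1 − (0.30 − 0.1167)/(1 − 0.1167) = 0.7925.

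**Step 3: what this does to power at f = 0.1.**

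| n complete | ρ = 0.5 | ρ = 0.8 |
|---|---|---|
| 9 | 0.10 | 0.19 |
| 20 | 0.18 | 0.44 |
| 31 | 0.28 | 0.67 |
| 40 | 0.37 | 0.80 |
| 56 | 0.51 | 0.93 |
| 70 | 0.63 | 0.98 |

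The effect-size metric matters. If 0.1 meant eta-squared, then f² = 0.1/0.9 = 0.111. At ρ = 0.5 power would be 0.75 at n = 9, 0.99 at n = 20 and essentially 1 at n = 56.

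**Step 4: precision, whatever the effect size.** The 95% half-width for a mean change is t(0.975, n−1)/√n in units of the SD of change: 0.77 at n = 9, 0.27 at n = 56, 0.24 at n = 70.

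**Step 5: data left unused.** With attrition linear over six months and 30% of the remaining assessments missing, the follow-up reports number Σ 100(1 − 0.2t/6) × 0.7 for t = 1 to 6, which is 371. If 9.4 children are complete, the analysis uses 9.4 × 6 ≈ 56 of them. This is the extreme, independent case.

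**The case against.** Several counter-arguments have force.

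- **Most of the sample would be lost.** A reader might infer this, but the article does not settle it. It follows for most per-assessment readings. If the 30% counts children, 56 or 70 of 100 stay in, and strong clustering within children also leaves about half.
- **The completers are a healthier, more compliant group.** This too is tempting, but it depends on why data are missing, which is unknown. Parents and healthcare professionals may report as proxies (Patient recruitment; Parent's involvement; HCP's involvement), which could reduce illness-related gaps. Selection is a risk, not an established fact.
- **The plan already deals with missingness.** It lists real steps: the seen/not-seen comparison, sensitivity analysis, power re-evaluation and mechanism checks. They describe the problem, but none changes who enters the main analysis.
- **The complete-case rule is inferred.** This is true. It follows from the classical form of the named methods; imputation could stand in a document not shown, and some rank-based longitudinal methods accept incomplete series. What remains is that the article names its methods, and as named they sit badly with its own missing-data figures.
- **The month-specific ANOVAs are also defective.** The documents do not support this. Each uses one value per child, needs no complete series and is not invalidated by within-child correlation.
- **Consequence.** The primary outcomes are feasibility rates, usability scores and qualitative data. None rests on these tests, and the strengths and limitations leave effectiveness to future randomised trials.

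**Conclusion.** The point holds as a mismatch between method and expected data. Taken in their classical form, the named methods would use between about 7 and 52 of 100 children if the 30% is per assessment, 56 if per child after attrition, and 70 if per child including attrition. With f = 0.1, power at 9 children is 10% to 19%, and at 56 it is 51% to 93%, for ρ from 0.5 to 0.8. So whether the stated 90% survives turns on three things the article leaves open: the meaning of the 30%, the correlation and the effect-size metric. Bias from selection is possible if data are not missing completely at random.

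The count of seven applies to the monthly questionnaires. It does not describe in-game symptom reporting, and parents give a baseline on only a subset of measures. The affected outcomes are secondary; this is a should-fix.

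**What to change.** 1. Make the main analysis of each monthly questionnaire outcome a linear mixed model for repeated measures, with month as a categorical effect and all observed visits included. Name a simpler covariance as fallback, because an unstructured one for seven visits has 7 × 8/2 = 28 parameters and may not converge. Multiple imputation is an acceptable alternative.
2. Analyse child and parent quality of life with a joint mixed model, or with imputed data. Keep the covariance structure modest: a fully unstructured one over 14 measures would have 14 × 15/2 = 105 parameters from at most 100 families.
3. Keep the complete-case ANOVA and MANOVA as sensitivity analyses.
4. State what the 30% means: per child or per assessment, and with or without attrition.
5. The subgroup ANOVAs at baseline, month 3 and month 6 may stay.

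The cost is analysis wording and some programming, with no new data. The mixed model and standard multiple imputation rely on data being missing at random. The sensitivity analysis already planned should probe that assumption.

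### The planned check for data missing at random cannot be made from observed data, and no named analysis covers children who stop reporting because they worsen

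*Protocol article*

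**What the plan says.** The Data analysis section of the protocol article treats attrition and missing data in one paragraph.

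- **Attrition.** Its effect is to be judged by methods from a cited source. The examples given are a baseline comparison of participants who were and were not followed up, a sensitivity analysis without further description, and "re-evaluation of the power of the study with the attained sample size".
- **Missing data.** Their impact is to be evaluated according to the importance of the variables. The paragraph then closes: "Checks for data ‘missing at random’ and ‘missing completely at random’ are going to be performed".

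The same section assigns change over time in the children's outcomes to repeated measures ANOVA or a non-parametric equivalent. The Sample size calculation section assumes 20% attrition and 30% missing data for 100 children with a baseline and six monthly measures. It does not say how the two rates combine.

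Other sections supply related information. Parents and healthcare professionals may complete questionnaires as proxies (Patient recruitment; Table 3, R1 and R5; the main usage phase for healthcare professionals). Table 4, H3, lets healthcare professionals update disease status and treatment goal through the study.

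**The concern.** The sentence treats two different things as the same kind of check. Missing completely at random has consequences that can be seen: missingness should be unrelated to site, age, earlier scores and so on. If it is related to them, the assumption is contradicted. Missing at random says that, given what was observed, missingness does not depend further on the unreported value. Testing that would need the unreported values.

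The distinction matters in this population. The children are on anticancer treatment, symptoms are reported mainly while playing a game, and quality of life is reported monthly. Feeling worse is a plausible reason not to play or report. If that happens after baseline, a comparison of baseline characteristics need not show it. Mean quality of life may then look better, and symptom burden lower, than it is. An apparently passed check could be cited to set this possibility aside.

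The planned longitudinal method adds to the problem. Repeated measures ANOVA in its standard form drops children with an incomplete series, which generally needs something close to missing completely at random. Even data that truly were missing at random would not justify it.

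**Working it through.** **Inputs from the Sample size calculation section:** 100 children; 7 measures (baseline plus 6 monthly); attrition 20%; missing data 30%. The plan gives no combined missing share, so there is no figure of its own to reproduce here. Its power statement is a separate matter on which this point does not rest.

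**Step 1: share of month-6 values missing.** Three readings are open:

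- The 30% already includes attrition: 30%.
- The 30% applies to retained children: 1 − (1 − 0.20) × (1 − 0.30) = 1 − 0.56 = 44%.
- The two rates are added: 20% + 30% = 50%.

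**Step 2: why the check cannot work.** Take the 44% reading, so 56 of 100 children report at month 6. Suppose in case A that the 44 missing values have the same mean as the 56 observed, and in case B that they are on average 0.5 SD worse. The 56 observed values, and every earlier and baseline value, can be identical in both cases. Any check computed from them returns the same answer, yet the true month-6 means differ by 0.44 × 0.5 = 0.22 SD.

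**Step 3: size of the possible bias.** Let m be the missing share and delta the amount by which missing values are worse than observed ones. The full mean is then (1 − m) × observed mean + m × (observed mean − delta), on a scale where higher is better. The observed mean is therefore too favourable by m × delta. The deltas are assumptions; the documents give none.

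| Assumed delta | m = 30% | m = 44% | m = 50% |
|---|---|---|---|
| 0.2 SD | 0.06 | 0.09 | 0.10 |
| 0.5 SD | 0.15 | 0.22 | 0.25 |
| 0.8 SD | 0.24 | 0.35 | 0.40 |

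This is the bias of the month-6 mean among those who report. It is not the bias of the repeated measures test, and it takes no account of proxy completion.

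**Step 4: a second route to the size.** A simulation with 56% observed let the odds of reporting fall by a factor of 1.5, 2 or 3 for each SD of worse current symptoms (also assumptions). The observed mean was too favourable by about 0.17, 0.27 and 0.39 SD. Dividing by 0.44, these correspond to deltas of about 0.4, 0.6 and 0.9 SD, so the deltas in the table do not need extreme behaviour.

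**Step 5: what repeated measures ANOVA would retain.** Take the reading in which 30% applies to retained children. If missed reports are independent between visits, children with all 7 measures number 100 × 0.8 × 0.7^7 = 6.6, about 7. With a complete baseline the figure is 100 × 0.8 × 0.7^6 = 9.4, about 9. If instead the same children miss every report, 100 × 0.8 × 0.7 = 56 remain. Independence is an assumption, so the plausible range is wide.

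**The case against.** A reader might infer that the risk goes wholly unexamined. The documents do not support that. The plan has an attrition comparison, a sensitivity analysis and an evaluation of the impact of missing data. Participation, adherence and premature discontinuation are primary outcomes, with interviews and focus groups on barriers and engagement. Proxy reports and recorded disease status can show something of what happened to children who fell silent. What stands is narrower: none of these is tied to the values that were not reported.

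A second objection is that an article leaves detail to the full protocol or analysis plan. That is right, and the brevity of the sensitivity analysis is not in itself a fault. The missing-at-random check is different. It is a positive commitment, and further detail elsewhere could not make it feasible.

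Third, the checks could be read loosely as asking whether missingness depends on observed variables, and no rule says that a pass permits missingness to be ignored. The loose reading would be sound practice, but it is a check against missing completely at random, which the sentence names separately. That a pass would be misused is a possibility, not something the plan states.

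Fourth, a reader might take 44% as the plan's own figure. It is one of three readings. Nor should much be made of the power re-evaluation: the text ties it to the attained sample size, does not say the observed effect will be used, and does not suggest that power replaces interval estimates.

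**Conclusion.** The point holds as an error in a stated rule: observed data cannot establish missing at random, so that half of the planned checks should go. No named analysis addresses children who stop reporting because they deteriorate after baseline.

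The size depends on two unknowns. One is the missing share, for which the planning rates allow 30% to 50% at month 6. The other is how much worse unreported values are, which is assumed. Across deltas of 0.2 to 0.8 SD the observed month-6 mean would be 0.06 to 0.40 SD too favourable. Whether any such bias will occur cannot be known from the documents.

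The weight is moderate. Quality of life and symptom scores are secondary outcomes, the study is an uncontrolled feasibility study, and the article leaves effectiveness to future randomised trials.

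**What to change.** 1. Delete the check for missing at random. Keep a check against missing completely at random, and describe predictors of missing reports: previous score, site, age, and disease status recorded by healthcare professionals.
2. Analyse change over time with a likelihood-based mixed model that uses all available reports, in place of repeated measures ANOVA. State missing at random as its assumption, not as a finding.
3. Specify the sensitivity analysis as delta-adjusted multiple imputation for PedsQL and SSPedi. Impute under missing at random, then make the imputed values worse by, for example, 0.2, 0.5 and 0.8 SD. Report the tipping point at which the conclusion changes, and use proxy reports where available to judge which shifts are plausible.

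The cost is a changed longitudinal model, which is more than a wording edit, and one extra sensitivity analysis. No new data need be collected.
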